The recruitment started in December 2020 and is ongoing. Sample size has been determined by a power analysis allowing a comparison between the four groups. The sample size calculation was based on a repeated measures ANOVA (“between factors”). Alpha was set at 0.05, power at 90%, the standardized effect size at 0.3 and the expected correlation between repeated measures at 0.6. These coefficients were successfully used in our previous studies (Grégoire et al., 2017, 2020a). As there will be four groups and four measurements times, a total of 116 patients will be needed according to this analysis. Based on our previous experience with a similar design, we expect a 20% drop-out rate, leading to a sample of 140 patients (35 in each condition; Grégoire et al., 2020a). As our group sessions will include approximately 10 persons, we will then aim at recruiting 40 participants in each condition (i.e., four groups of 10 participants in hypnosis, MSC meditation, and SICT groups and 40 participants in the control group), for a final sample of 160 participants. Participants will have the opportunity to choose the intervention in which they want to participate. Most of the participants already have a strong preference for one of the three interventions when contacting us. However, each interested person who fill the inclusion criteria will be asked to watch a short video we made to explain the three interventions and the aims of the study.^1^ This allows every participant to receive standardized information about the study and to make or confirm their choice of intervention. However, once 40 participants have been recruited in a condition, it will not be possible for other interested persons to be included in this condition. These persons will be proposed to integrate the control group or another active condition.

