The three interventions will take place in Liège (hypnosis, SICT) and Brussels (MSC meditation). During the entire study duration, each participant will benefit from usual care, including medical care, oncological revalidation, and individual psychological help if necessary. Although no adverse event has been reported in our previous studies on hypnosis with patients with cancer or chronic pain (Grégoire et al., 2017, 2018b, 2020a; Bicego et al., 2021b) and clinical practice, it could be possible that a patient feels uncomfortable during the exercises. In this case, they will have the possibility to stop the session and their participation in the study. The therapist or the experimenter can also propose a meeting to discuss their difficulties and, if necessary, suggest a meeting with a psychologist or physician with whom we collaborate. Any reason for drop-out will be consigned. Adherence to the study is fostered by the facts that all participants are volunteers and motivated to participate and that the assessments can be mainly done at home and require only three travels to the hospital during the whole study. Several reminders will also be sent to the participants who forget to answer the questionnaires in time and who did not ask to quit the study.

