### Statistical Analyses

Baseline (T0) demographic, medical, and psychological data will be compared between groups to test for initial groups equivalency using inferential statistics, including ANOVAs and chi-square tests. Normality of data will be checked using Shapiro–Wilk test. Group-by time changes, and pre- and post-assessment comparison of each variable within each group will be assessed using repeated measures MANOVA followed by post hoc comparisons, on the participants who completed all the needed assessments points. Hierarchical linear regressions will be conducted to investigate the factors associated with the evolution of our main outcomes. All tests will be two-tailed, and the alpha will be set at 0.05. For EEG data analysis, MATLAB, EEGLAB, FieldTrip, Brainstorm, and in-house MATLAB and Python modules will be used. EEG signal will be preprocessed as in our previous works [downsampling, epoching, filtering, removing noise (notably using ICA), channels interpolation, re-referencing; Carrière et al., 2020; Thibaut et al., 2021]. EEG markers will then be extracted: spectral (e.g., power spectrum density), connectivity (e.g., weighted symmetrical mutual information), complexity (e.g., permutation entropy; Engemann et al., 2018). We will also apply graph theory connectivity measures to further assess changes between brain regions (Chennu et al., 2017; Carrière et al., 2020; Thibaut et al., 2021). Results will be corrected for multiple comparisons and considered significant at *p* < 0.05. Statistical analyses will be performed after all data have been collected for T2, then for T3 and T4.

All participants will be informed by e-mail about the final results of the study. Scientific publications and presentations will also be planned.

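### The main analysis is limited to completers although 20% drop-out is expected, so it discards observed data and can bias within-group changes and, if drop-out differs between arms, the group contrasts

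*Protocol article*

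**What the plan says.** All references are to the protocol article.

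- **Statistical Analyses.** Group-by-time changes and the pre/post comparisons within each group are assessed by "repeated measures MANOVA followed by post hoc comparisons, on the participants who completed all the needed assessments points". Analyses are staged: one once T2 is complete, others later. The section names a T4 that the visit schedule does not define.
- **Recruitment.** The required sample is 116. Then "we expect a 20% drop-out rate, leading to a sample of 140 patients", rounded up to 40 per condition "for a final sample of 160 participants".
- **Design and Table 1.** Questionnaire outcomes are collected at T0, T1 (end of intervention), T2 (3 months) and T3 (1 year). Participants choose their condition and know it. The three interventions differ in structure and intensity, and controls attend none of them.
- **Interventions, closing paragraph.** A participant who feels uncomfortable during exercises is told that "they will have the possibility to stop the session and their participation in the study". Reasons for leaving are recorded and reminders are sent, but neither is given a use in the analysis.
- **Measurement Points.** The online forms do not accept blank answers. This prevents missing items, not missed visits or withdrawal.

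The article describes no analysis that uses partial follow-up.

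**The concern.** The completer restriction is written into the article, so it is a choice made and not a detail left to an unseen analysis plan. It has three consequences.

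1. A participant seen at T0, T1 and T2 but not at T3 contributes nothing to an analysis that needs all four visits, although three valid assessments exist.
2. With staged reports, the T1 effect may be estimated on one completer set in the T2 report and on a smaller one in the T3 report.
3. Completers are a selected group if leaving is related to how a participant is doing. The planned within-group pre/post tests then describe that group and not those enrolled. The group contrasts are distorted as well if the selection works differently between arms.

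Different selection by arm is plausible here. Arms are chosen, open and unequal in burden. Only the active arms contain exercises that might cause discomfort. Controls are offered an intervention after the study, which gives them a different reason to stay. The Discussion expects benefits to hold or grow at follow-up through continued practice, and selective retention of responders could imitate that pattern.

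**Working it through.** **1. Reproduce the planned sample size.** Inputs from Recruitment: "Alpha was set at 0.05, power at 90%, the standardized effect size at 0.3 and the expected correlation between repeated measures at 0.6", four groups and four measurement times, between-factors repeated measures ANOVA. Read 0.3 as Cohen's f.

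λ = f² · N · m / [1 + (m − 1)ρ], with 3 and N − 4 degrees of freedom.

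For N = 116: λ = 0.09 × 116 × 4 / 2.8 = 14.91, power 0.905. The smallest N reaching 90% is 115 (0.902), which becomes 116 in four equal groups. The stated 116 is reproduced.

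**2. Number excluded, and power.** 0.20 × 160 = 32, leaving 128. Then λ = 0.09 × 128 × 4 / 2.8 = 16.46 and power is 0.933. The stated 140 matches 116 × 1.2 = 139.2 rounded up, whereas dividing by 0.8 gives 145; 160 covers both. The completer rule does not cause a power shortfall for the planned test.

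**3. How bias arises.** In arm g, completers' mean change equals the true change plus a selection shift s(g). A within-group change is therefore wrong by s(g), and the active-versus-control contrast by s(active) − s(control). The contrast is unbiased if the two shifts are equal, even when neither is zero.

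**4. Illustration.** Assumptions, none taken from the article except ρ = 0.6: outcome SD 1; equal correlation between all visits; true improvement over control 0.50 SD at T1 to T3; 20% drop-out per arm after T1; log-odds of drop-out linear in the T1 change, with odds ratio 1.65 or 2.7 per SD of that change in the worse direction.

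Large-sample simulation gives a T1 shift of about 0.087 (odds ratio 1.65) or 0.155 (2.7) in an arm with this mechanism. The T3 shift should be half as large, because the slope of the T3 change on the T1 change is (1 − ρ) / [2(1 − ρ)] = 0.5. The simulation agrees: 0.043 and 0.077. Doubling the log-odds slope gives T1 shifts of 0.156 and 0.234.

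| Drop-out after T1 | Completers, T1 contrast | Completers, T3 contrast |
|---|---|---|
| Related to response in active arm only | 0.59 to 0.65 | 0.54 to 0.58 |
| Same relation in both arms | 0.50 | 0.50 |
| Log-odds slope twice as steep in control | 0.42 to 0.43 | 0.46 to 0.47 |
| Completely at random | 0.50 | 0.50 |

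The third row follows from the shifts: at T1, 0.50 + 0.087 − 0.156 = 0.43 and 0.50 + 0.155 − 0.234 = 0.42.

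In the second row the contrast is right but the within-group results are not. The active arm shows 0.59 to 0.65 at T1 instead of 0.50, and controls show an improvement of 0.09 to 0.15 where the truth is zero.

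In all four rows, a likelihood-type analysis that keeps the T0 and T1 data of those who leave returns 0.50.

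**5. Drop-out before T1.** If the same active-arm participants leave during the intervention, only T0 is observed. Completers again give 0.59 to 0.65 at T1, and the likelihood-type analysis gives 0.57 to 0.63. Little is recovered.

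**The case against.** Several points on the other side are sound and limit the claim.

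- **Needed visits.** The rule concerns the assessments that an analysis needs. With staged analyses, the natural reading is that someone with T0 to T2 stays in the T2 analysis and is lost only from the later one. A reader might infer that anyone missing T3 is removed from the study's results altogether; the wording does not support that.
- **Direction.** A reader might infer that completers in the active arms are those who benefited, so that effects are overstated at every time point. The article gives no drop-out by arm or by response. Under Recruitment, people whose chosen condition is full are offered control or another active condition, so response-related drop-out among controls is plausible too and would understate the effect.
- **Completely at random.** It is tempting to say that a completer analysis is unbiased only under that condition. For the between-group contrast this is too strong, as the second row of the table shows.
- **Power.** The sample was inflated for drop-out, so the loss of 32 participants is planned for. This stands. Inflation does not remove bias, however.
- **The remedy.** The discomfort that the article describes arises during exercises, before T1, where a mixed model helps much less. This also stands. It reduces the gain but gives no reason to prefer completers.

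What remains is a stated rule that discards observed data and needs a stronger assumption than the obvious alternative.

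**Conclusion.** The concern holds in conditional form. The rule excludes the partial data of up to 32 of 160 participants, most clearly from the final T0 to T3 analysis, and lets the T1 estimate rest on different people in successive reports. Within-group changes are biased if drop-out depends on response. Group contrasts are biased, upwards or downwards, if that dependence differs between arms.

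The figures of 0.59 to 0.65 SD at T1 and 0.54 to 0.58 at T3, against a true 0.50, belong to one assumed scenario: active-arm drop-out after T1 linked to observed T1 change, and random drop-out in control. They show that the bias can matter. They do not estimate its size in this trial, and other scenarios give no bias in the contrast or bias the other way. The article also does not say when the 20% would occur. The case rests on bias and discarded data, not on power.

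**What to change.** In Statistical Analyses, make the primary analysis a linear mixed model for repeated measures:

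- all observed T0 to T3 assessments from all enrolled participants, analysed in the condition they entered;
- group, time and group-by-time terms with unstructured covariance;
- active-versus-control contrasts at T1, T2 and T3 from this model.

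Keep the completer MANOVA as a sensitivity analysis. The mixed model is valid under missing at random and recovers little for participants who leave before T1. A sensitivity analysis under missing not at random, such as a delta shift, is therefore desirable, but it is optional and could sit in the analysis plan.

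The cost is a change of wording and slightly more analysis work. No further participants or data are needed.

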## Discussion

Based on previous studies showing the benefits of different mind–body interventions, such as hypnosis and meditation, on cancer patients’ quality of life (Spiegel, 1985; Kim et al., 2013; Cramer et al., 2015; Carlson et al., 2017; Grégoire et al., 2017, 2020a; Ngamkham et al., 2019; Suh et al., 2021), and on the growing interest of these patients for such interventions, we designed a longitudinal controlled study assessing the benefits of three mind–body group interventions based on non-ordinary states of consciousness: hypnosis, MSC meditation, and SICT. Our aim is to investigate the short- and long-term effects of these interventions on physical and psychological symptoms of post-treatment oncological patients and to investigate their phenomenological experiences, their neurophysiological correlates, and their mechanisms of action. Our wish is also to include a variety of cancer diagnoses to address a major gap in the scientific literature: the lack of data about the effects of psychosocial interventions on cancers other than breast cancers.

Based on the existing scientific literature, our previous studies, and preliminary data (not published), we made several hypotheses:

**Hypnosis, MSC meditation, and SICT will have positive overall benefits on the quality of life of cancer patients**, with increased effects over time. More specifically, we expect that the three interventions will have superior positive effects on the patients’ quality of life than the control group. We expect that these effects will be significant right after the intervention (T1) and will stay stable or increase at 3- and 12-month follow-up (T2 and T3) due to continued practice. Moderate difference might be observed between the three intervention groups. For example, SICT could impact more the body-related variables (e.g., pain and fatigue) as it involves the body more directly (e.g., in the induction process). We expect that a small improvement will be achieved in the control group as well, but much weaker than in the three intervention groups.**Phenomenological experiences will change over time and will be intervention-dependent**. We hypothesize that over time and in the three intervention groups, phenomenology will become more joyful and richer. As the phenomenology of hypnosis, MSC meditation, and SICT has been very little studied, we do not have any specific hypothesis concerning the phenomenological differences between the three interventions. Our analyses are exploratory. We however expect that the phenomenology will change in each intervention group between the different measurement times, as the participants are expected to continue to practice regularly after the intervention. We do not expect any major evolution of the phenomenological experiences in the control group.**Neurophysiological changes will be different between the three intervention groups**. We hypothesize that neurophysiological changes will vary according to the intervention and that they will evolve over time, in response to the continued practice of the participants after the intervention. Previous studies showed increased theta power and changes in gamma activity during hypnosis (Vanhaudenhuyse et al., 2020) and increased alpha and theta power, during meditation (Lomas, 2015; Brandmeyer et al., 2019). We hypothesize to observe the same patterns in our study. We do not expect any evolution of neurophysiology in the control group. We also expect differences in neurophysiological correlates of resting state, depending on patients’ clinical outcomes, especially long-term ones. For example, we could expect slower activity if patients are feeling less anxious.**We will be able to confirm, at least in part, the biopsychosocial model of hypnosis**, and MSC meditation and SICT responsiveness mechanisms will be in part similar to the ones implied in hypnosis responsiveness. We also expect other potential factors (linked to body physiology: temperature, ECG, EMG, breathing) to correlate with hypnosis, MSC meditation, and/or SICT responsiveness.

Participants are not aware of the specific hypotheses of our study. However, they have a general idea of the study aim, as the flyers and posters used for the recruitment underlined the fact that the purpose of each intervention is to improve their quality of life.

There are some limitations of our study. First, only patients who have finished their active treatments for less than a year can participate in the study. It is possible that patients who finished their treatments longer ago, or who are still in treatment, will be willing to participate. The same limitation applies for most of our inclusion criteria: some patients with brain tumor, or who are currently practicing hypnosis or meditation for example, could be interested in the study, and will not be able to participate. It is then possible that these inclusion criteria will impact the recruitment process and our results. However, they were chosen in order to minimize the baseline differences in our sample. Another limitation is linked to the profile of our participants. As our study takes place in Belgium, our participants will mainly come from Belgium or France or maybe French-speaking areas of other bordering countries. This means that all our participants will come from western and industrialized areas, which could induce some similarities among them. Our three interventions are also proposed in a group setting, which could discourage some people to participate as they could be uncomfortable in sharing their experience and thoughts with others. In addition, the therapists involved in our study could also be considered as a potential bias. Indeed, some of them are recognized as international experts in their discipline, and the fact that they will lead the group sessions is likely to impact the recruitment process, with more patients wanting to participate in their interventions. Finally, the design of our study could be considered as a limitation. First, our study will not be randomized, even though randomized-controlled trials are generally considered the gold standard for research aiming at assessing the effectiveness of an intervention (Hariton and Locascio, 2018). This preference-based design was chosen because we did not find it relevant for a patient who wants to participate, for example, in the hypnosis intervention to be obliged to participate in another intervention. Indeed, patients who can chose their treatment have more motivation and a greater adherence (King et al., 2005; Preference Collaborative Review Group, 2008; Sedgwick, 2013; Bicego et al., 2021a). We also chose this design based on our clinical observations. After a generally long cancer journey, where patients rarely had the opportunity to make any choice and had to endure several intense treatments and their side effects, it seemed important to us to allow them to finally take back the control over their care and choose the intervention they want to participate in. In addition, preference-based and pragmatic trials are more and more represented in scientific studies when the aim is to assess the effectiveness of an intervention for the participants who chose it, rather than determining the best treatment option (Kowalski and Mrdjenovich, 2013), or to assess the effectiveness of the intervention in real-life conditions (Patsopoulos, 2011). Second, the designs of the three interventions are different in terms of duration and frequency. As explained above, we decided to use these designs because they have been shown to be acceptable and effective in our practice with volunteers and patients. As the main aim of this study is not to investigate how each intervention allows an improvement of the patients’ quality of life, using different intervention designs seems understandable and acceptable. If our results are conclusive, future research should continue to investigate these three interventions and their mechanisms of action by standardizing their designs.

In conclusion, this project is particularly original, timely relevant and innovative. First, it will allow to adequately evaluate the short- and long-term effects of the interventions to improve the quality of life of a mixed population of patients who often suffer from intense and debilitating long-lasting cancer-related symptoms, along with behavioral, phenomenal and neurophysiological changes. This could lead to an improvement of mind–body interventions in oncology settings in the future, along with a better understanding of hypnosis, meditation, and SICT phenomena and their impact on quality of life. We could also imagine proposing these mind–body interventions to other clinical populations in the future (e.g., patients with chronic pain). Second, combining phenomenology and electrophysiology with rigorous methodology will be an asset to dive deep into the cognitive and brain functions related to hypnosis, meditation, and SICT, including their impact on physical and psychological symptoms.

## Ethics Statement

The studies involving human participants were reviewed and approved by Hospital-Faculty Ethics Committee of Liège. The patients/participants provided their written informed consent to participate in this study.

## Abbreviations

ANOVA: Analysis of variance
BFI: Big Five Inventory
CERQ: Cognitive Emotion Regulation Questionnaire
CEQ: Creative Experiences Questionnaire
CHU: “Centre hospitalier universitaire” (University Hospital)
CRF: Cancer-related fatigue
ECG: Electrocardiogram
EEG: Electroencephalogram
EMG: Electromyogram
FACT-Cog: Functional Assessment of Cancer Therapy - Cognitive Function
GDPR: General Data Protection Regulation
HADS: Hospital Anxiety and Depression Scale
Hrs: hours
ISI: Insomnia Severity Index
MAC: Mental adjustment to cancer
MCQ: Memory Characteristics Questionnaire
MEQ: Mystical Experience Questionnaire
MFI: Multidimensional fatigue inventory
MPFI: Multidimensional Psychological Flexibility Index
MSC: Mindful self-compassion
SICT: Self-induced cognitive trance
VAS: Visual analogue scale
